Our preliminary data demonstrate the feasibility and acceptability of practicing Qigong for non-Hispanic White adults with SCI-related neuropathic pain with promising results in terms of pain relief, SCI-related symptoms, improved function, and mental well-being after Qigong practice [14,25]. Eighteen participants completed the study (18/21 enrolled; 86% retention), with 100% adherence to all study components, and 12 participants completed the 1-year follow-up. We enrolled a representative sample of women with SCI (6/18, 33%), adults 65+ years of age (7/18, 39%), living in rural areas (6/18, 33%), Veterans (3/18, 17%), adults in socioeconomic distress (12/18, 67%), and below the poverty threshold (3/18, 17%) [6,14,28]. Even though we recruited nationwide, all participants were non-Hispanic White, pointing to the need for more encompassing recruitment strategies. Participants practiced at home, at least 3 times per week for 12 weeks (123 minutes), with a Qigong video accessible via the internet (ie, the same video as proposed below). Our results showed feasibility and adherence to the intervention (138% of the required intensity of Qigong practice, representing 170 minutes) and no study-related adverse events.

However, despite these promising data, three additional key elements need to be addressed before performing a larger phase II effectiveness clinical trial: obtaining data from adults with SCI with health disparities on (1) feasibility and acceptability of participating in a Qigong study, (2) feasibility of the study design (including an active comparison group) and adherence to the interventions, and (3) obtaining objective outcome measures.

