### Interventions

Two active interventions are proposed, with different “active ingredients.” More information about the interventions is given below.

The Qigong introduction class will be taught over Zoom by a Spring Forest Qigong-certified instructor. Then, participants will practice Qigong at least 3 times per week for 12 weeks with the “Five Element Healing Movements” online video with streaming access from any computer, iPad, or smartphone device, so participants can practice at home or any location with an internet connection. More details about the content of the Qigong practice can be found in our published protocol paper of the Qigong pilot study in adults with SCI-related neuropathic pain [25]. Participants log in with a unique study identification number and password onto the Spring Forest Qigong website to access the video and practice at least 3 times per week for 45 minutes per session. Their practice (time and duration of access) will be logged automatically and sent to the principal investigator ([name]), who is level 5 (of 5 levels) in the Spring Forest Qigong curriculum, and a certified practice group leader.

Once a month, the Spring Forest Qigong-certified instructor will do a Qigong session 1:1 with each participant over Zoom to monitor their practice, address questions, demonstrate movements, and give guidance as needed to ensure quality control of the practice. We will use the recording option on the Zoom platform, and the video will be stored on our server, called the University of Minnesota secure box.

The active comparison group will receive a daily text or email message (depending on the choice of the participant) linking them to a 2-minute online Qualtrics survey to answer questions related to their pain intensity level, medications taken that day, activities that helped or hindered the pain, and free text on what they did that day that mattered to them. There are no educational or lifestyle advice components, and they will not receive any guidance on any of the active ingredients given in Qigong (ie, breathing, meditation, and meditative movements). Pain management has been examined through an app in multicenter trials and feasibility studies and is being used in large health care systems in Canada [38].

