#### Feasibility Benchmarks

Our feasibility markers are consistent with models and guidelines for intervention development (Table 2) [29,42]. Based on prior publications [43-46], we will assess the following a priori feasibility markers.

**Table 2 table2:** Feasibility benchmarks.

	Feasibility item and details	Benchmark (go/no-go criteria)
Recruitment and enrollment	Assess recruitment rates (screens and enrollment per trimester, sex, and racial outcomes). Evaluate the recruitment rate for complete and incomplete SCI^a^. We aim to recruit 40 participants between mid-year 1 and year 2.	The proportion of potential participants contacted who agreed to participate: 80% is excellent and 70% good. Ratio of complete/incomplete SCI. We estimate recruitment of 30%-40% of adults with complete, 60%-70% with incomplete SCI. Reasons for (not) participating and information collected during focus groups or interviews will help delineate facilitators and barriers to participation, including computer or internet access.
Feasibility and acceptability of the study design	Attrition rates in the Qigong or pain management survey groups.	Proportion of people withdrawing from the interventions. Dropout due to unrelated reasons will count as part of the general attrition. A proportion of 90% is excellent, and 80% good.
Feasibility, adherence, and acceptability of the Qigong practice	Assess intervention adherence, average Qigong practice, at least 3×/week (123 minutes), pain management surveys (daily), and satisfaction with the Qigong practice or pain management surveys. Identify facilitators and barriers to practicing Qigong at home or completing the pain management surveys.	Weekly and monthly check-ins (reporting minutes/week of practice) to identify facilitators and barriers to pain management surveys or practicing Qigong. The Qualtrics website (for pain management surveys) or Spring Forest Qigong website (for Qigong practice) logs time and duration of video access. A Spring Forest Qigong-certified instructor will do a 1:1 Qigong session with each participant via Zoom monthly for quality control and to give guidance. Feasibility: Excellent: >80% participants practice at least 2×/week; good ≥70%. For the pain management survey: completion of surveys at least 5 out of 7 days. Dropout due to lack of interest will be counted as general attrition: 10% dropout is excellent, 20% is good.

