#### Objective Measurements of Sleep, Activity, and Other Information, Obtained With a Consumer Device, the Fitbit Charge 6 Watch

Our primary data will be physical activity (minutes), heart rate (every second), stress level (heart rate variability–based), and sleep (minutes). Participants will install the Fitbit app with their account and use the OAuth 1.0a protocol on a University of Minnesota website (developed by coauthor [name]) to authorize Fitbit to transfer data directly to our University of Minnesota server. Participants will leave the Fitbit app open in the background so data can be transmitted to our server. In this way, we can monitor that data is being received and that the device is being charged. [name] has used this method successfully in several studies [64,65].

Virtual delivery of questionnaires related to assessments or check-ins will be organized through our secure University of Minnesota Zoom. Participants will be encouraged to complete all scheduled virtual visits and assessments. However, missed sessions will be allowed and recorded and will not be considered protocol deviations. We had 100% adherence to Qigong training, assessments, and weekly check-ins through Zoom in our prior Qigong studies (IRB# STUDY00005656; IRB# STUDY00011997) in those who completed the study. If an EMA survey, pain management assessment, or weekly or monthly check-in is missed, measures will be taken to get the information later. There are no stop criteria for missed sessions or missed testing. The clinical trial will be completely remotely delivered.

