#### Data Analysis

The demographic variables and other baseline characteristics, including sex, race, and ethnicity, will be summarized using descriptive statistics, including mean, median, SD, IQR, minimum, and maximum. Rate parameters for the feasibility markers will be estimated based on the participants who achieved each benchmark. All quantitative variables, including primary and secondary outcomes, will be summarized using descriptive statistics. For longitudinal outcomes, missing data will not be imputed. Mean and SD will be calculated for each outcome at each time point. Means and SDs of across-time changes (eg, pre- vs post-Qigong or pain management survey changes) and correlations will be estimated for all participants, each group, or stratum that will be used for sample size determination in future studies. Mediation analyses will explore potential mediators among variables measured with the Fitbit device for the relation between Qigong practice or pain management surveys and changes in neuropathic pain. Descriptive and feasibility data related to adults with health disparities will be investigated. Missing data will not be imputed. The % missingness will be tabulated for each time point by group, and the mechanism of missingness will be identified.

The qualitative variables (eg, focus groups, interviews, weekly and monthly check-ins) will be recorded, transcribed, and managed using NVivo (Lumivero). Coded units will be sorted into categories and analyzed for recurrent themes or patterns. Emerging categories will be reviewed for alignment with the quantitative findings. These findings will serve to reach conclusions on the feasibility, acceptability, and satisfaction of adults with SCI-related neuropathic pain in study participation and performing Qigong practice or completing pain management surveys. We will also report on conclusions relevant to adults with health disparities.

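### The only Qigong adherence go/no-go is set at two sessions a week, although the same table row and the Interventions section set three, so it can read excellent with nobody at the prescribed frequency

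*Protocol article*

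**What the plan says.** Three parts of the protocol article bear on Qigong adherence.

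- **Prescription.** The Interventions section says that "participants will practice Qigong at least 3 times per week for 12 weeks", and that they are to "practice at least 3 times per week for 45 minutes per session".
- **Benchmark.** In Table 2 (Feasibility Benchmarks), whose right-hand column is headed as go/no-go criteria, the adherence row describes its item as "Assess intervention adherence, average Qigong practice, at least 3×/week (123 minutes" per week. The scoring rule in the same row is "Feasibility: Excellent: >80% participants practice at least 2×/week; good ≥70" per cent. The survey group's threshold is completion on 5 of 7 days. Dropout for lack of interest is assigned to general attrition, which has its own grades: 10% is excellent and 20% is good.
- **Estimation.** The Data Analysis section states: "Rate parameters for the feasibility markers will be estimated based on the participants who achieved each benchmark".

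The Background describes the pilot, which used the same video, in these terms: "Participants practiced at home, at least 3 times per week for 12 weeks (123 minutes". It reports that pilot participants reached 138% of the required practice, or 170 minutes.

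**The concern.** Adherence to Qigong is a prespecified Aim 2 target, and the results are meant to support a later effectiveness trial. The designers of that trial will want to know what share of people assigned to Qigong carry out the practice as prescribed. The Table 2 row announces that it assesses practice at three sessions a week, but it grades a different and lower frequency without explanation. An excellent grade therefore says nothing definite about the practice the row names.

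Two related points affect how the adherence result can be read. The weekly minutes equated with three sessions differ between sections, so a percentage of required practice has two possible bases. The sentence on estimating rates identifies who counts as a success but not out of whom, so the same data could support different grades.

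**Working it through.** **1. Frequency scored against frequency prescribed.** Inputs: at least 3 sessions a week (Interventions; Table 2 item) and at least 2 sessions a week (Table 2 cut-off).
- Ratio: 2/3 = 66.7% of the prescribed frequency.
- Limiting case: all Qigong participants practise exactly twice a week. Share at 2 or more = 100%, graded excellent. Share at 3 or more = 0%. This needs no assumption about arm size or dropout.
- For comparison, the survey group's threshold is 5/7 = 71.4% of its daily schedule.

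**2. Weekly minutes.** Inputs: 45 minutes per session (Interventions); 123 minutes for three sessions a week (Table 2 and Background); 138% and 170 minutes (Background).
- Reproducing the article's own pilot figure: 1.38 × 123 = 169.7, or about 170. So 123 was the base of the 138%.
- From Interventions: 3 × 45 = 135 minutes. From Table 2: 123/3 = 41 minutes per session.
- Gap: 135 − 123 = 12 minutes, and 12/135 = 8.9%.
- Effect on a percent-of-required figure: 170/123 = 138%; 170/135 = 126%.
- Effect on the benchmark: none, because it counts sessions.

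**3. Denominator.** The article gives 40 participants in two groups but no allocation ratio, so 20 in the Qigong arm is an assumption. The Results section reports 8 dropouts among 36 recruited for Aim 2, both groups together: 8/36 = 22.2%. Applied to 20 this is 4.4, taken as 4. The table shows the smallest count that earns excellent (above 80%) when dropouts are left out, and what that count is as a share of all 20.

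| Dropouts | Remaining | Needed for excellent | Rate without dropouts | Share of all 20 |
|---|---|---|---|---|
| 0 | 20 | 17 | 85.0% | 85% |
| 2 | 18 | 15 | 83.3% | 75% |
| 4 | 16 | 13 | 81.3% | 65% |
| 5 | 15 | 13 | 86.7% | 65% |

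With 4 dropouts, the choice of denominator alone moves the result from below the 70% line for good to excellent. In that example attrition is 4/20 = 20%, which Table 2 grades as good. Both rows would then pass although only 65% of those randomised practised even twice a week.

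**The case against.** A feasibility threshold below the prescription is not a mistake in itself. The survey group's 5 of 7 days is also below its schedule, and by a similar margin. Table 2 says its markers rest on prior publications, which cannot be consulted here and may explain the choice. Weekly minutes are reported at check-ins and video access is logged, so practice at three sessions a week will be observable. The pilot's 138% suggests that nobody reaching three sessions is unlikely. All of this stands. It does not remove the gap: the row names one frequency, grades another and attaches no benchmark to the first.

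A reader might infer that dropouts are excluded, so that adherence is a completer rate. The documents do not establish this. Table 2 refers to participants without restriction, and counting someone under attrition does not remove them from the adherence denominator. The phrase "in those who completed the study" describes adherence in earlier studies and sets no rule for this one. The no-imputation statement concerns missing data and does not address logged practice. Dropout is also graded separately and would be visible: the pooled 22% to date is worse than the 20% that counts as good. What remains is that the stated estimation rule leaves the denominator open.

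A reader might also take the 123 versus 135 conflict as a route to a false excellent grade. It cannot be one, since the benchmark does not use minutes.

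**Conclusion.** The point holds in a limited form and is worth correcting. The firm part rests on the text alone: the only Qigong adherence go/no-go sits at two thirds of the frequency that its own row and the Interventions section state, without a reason. It can read excellent at 0% of the prescribed frequency. The minutes conflict is also plain, at 12 minutes a week. It matters only for reported minutes and for percentages of required practice (138% or 126% for the pilot's 170 minutes).

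The denominator part is conditional. It depends on dropouts being left out, which the article neither says nor rules out, on an arm of 20, and on applying the pooled dropout rate to the Qigong arm. Under those assumptions, 81% and 65% describe the same 13 people and fall on opposite sides of the go/no-go lines. The documents do not support the claim that the plan excludes dropouts or hides them.

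**What to change.** 1. Reconcile the Background, Interventions and Table 2 on session frequency, session length and weekly minutes. This review takes no position on which figures are right. If a frequency below the prescription is kept as a benchmark, give the reason in Table 2.
2. For all randomised to Qigong, with dropouts counted as non-adherent from when they stop, report the share reaching the reconciled prescribed frequency. Beside it, under its own label, report the share reaching the lower benchmark frequency. The sponsor's existing criterion is then still reported, and a reader can see what it does and does not show.
3. Reword the Data Analysis sentence so that each rate is the number achieving the benchmark divided by all randomised to that arm. Apply the same rule to the survey group.

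The change needs edits to Table 2, one sentence of analysis text and the conflicting figures. The website logs already record time and duration of video access, so no new data collection is needed. The drawback is that the adherence figure is likely to look less favourable.

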**Methods:**

For aim 1, a total of 40 SCI stakeholders—adults with SCI, caregivers, health care professionals, or other stakeholders who have experience with caring for adults with SCI—will be invited to attend community event meetings, one focus group, or an interview, where they will provide input on facilitators and barriers related to participating in a Qigong study. For aim 2, using a phase I randomized controlled trial design, 40 adults with SCI-related neuropathic pain (with at least 50% [n=20] having health disparities) will be randomized to a 12-week remotely delivered Qigong intervention (practicing at least 3×/week with the Spring Forest Qigong’s “Five Element Qigong Healing Movements” video), or a short daily pain management survey, completed on a smartphone, iPad, or computer + 6-month follow-up. Feasibility benchmarks, as well as patient-reported outcome measures and objective data from the Fitbit Charge 6 watch, will be collected during the study.

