## Methods

### Overall Study Design

For aim 1, we will hold community event meetings (ie, education and listening sessions) in town halls and health care settings for SCI stakeholders to share information about the research and hold listening sessions. We will organize focus groups and in-depth interviews using the Consolidated Framework for Implementation Research in the Twin Cities and in South Texas. We estimate we will have 3-5 attendees if on Zoom, and 5-8 attendees if in-person. We estimate holding 3 in-depth interviews with the most informative SCI stakeholders, to better understand the facilitators and barriers to remotely delivered Qigong practice, and identify which sociodemographic, behavioral, cultural, or structural factors facilitate or hinder participation in the study as a whole, including access to a computer, iPad, or smartphone and internet needed for Qigong practice or pain management through a Qualtrics survey, and remotely delivered questionnaires. If in person, the focus groups and interviews will be held in Minnesota (University of Minnesota–Twin Cities) and South Texas (University of Texas Rio Grande Valley [UTRGV]).

For aim 2, we will organize a feasibility phase I randomized controlled trial design where 40 adults with SCI-related neuropathic pain with at least 50% (n=20) with health disparities (racial or ethnic minorities, Veterans, or adults living in rural, underserved areas) are randomized to (experimental group) a Qigong introduction class and a 12-week remotely delivered Qigong intervention, with a 6-month follow-up, or (active comparison group) they complete daily 2-minute surveys to manage their pain sent through Qualtrics, with a 6-month follow-up.

Randomization will be generated by an independent biostatistician. The outcome assessors and the biostatistician on the study will be blinded to the group allocation. We have registered this clinical trial with the National Institutes of Health (NIH) clinical trials registry. Our feasibility pilot trial follows the guidelines according to the Obesity-Related Behavioral Intervention Trials model [29] and NCCIH [30]. Based on the guidelines, we developed aims, protocol, and the following a priori feasibility benchmarks to rigorously test the methodology and feasibility of the intervention before a larger effectiveness clinical trial is conducted.

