Feasibility of adhering to the collection of quantitative measures	% Adherence in completing all assessments during the study and in the monthly follow-up phase until 6 months postintervention. % Adherence to wearing the Fitbit Charge 6 smartwatch and sending the data through their Fitbit app on their smartphone.	Feasibility is ‘excellent’ when none of the Zoom questionnaires, EMA^b^ surveys, or weekly and monthly check-ins are fully missing in >25% of the participants. Excellent adherence: data from the Fitbit app at least 70% of the time and wearing the Fitbit Charge 6 at least 5 out of 7 days/week for at least 7 hours/day (≥80% excellent; ≥70% good).
Program satisfaction	3-item Client Satisfaction Scale [47]. Ask about their intent (and frequency) to continue the Qigong practice or pain management surveys after the 12-week intervention program.	Excellent satisfaction if ≥75% of the participants score above the scale midpoint; and good if ≥70%. Our benchmark is ≥70% of the participants intend to continue the Qigong practice or pain management surveys after 12 weeks.
Program safety	Assess adverse events (IRB^c^+GCP^d^ reporting guidelines) and report adverse events via ACTTION^e^ recommendations [48,49].	Excellent safety: no study-related adverse events; good if there are minimal and mild adverse events (eg, muscle soreness) linked to Qigong practice in max 10% of participants, or any adverse events with the pain management surveys. We will ask about adverse events during the weekly and monthly check-in calls.

^a^SCI: spinal cord injury.

^b^EMA: ecological momentary assessment.

^c^IRB: Institutional Review Board.

^d^GCP: Good Clinical Practice.

^e^ACTTION: Analgesic, Anesthetic, and Addiction Clinical Trial Translations, Innovations, Opportunities, and Networks.

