Given that Qigong involves slow, gentle movements in standing, sitting, or lying positions, we do not expect any study-related adverse events from the treatment, similar to our experience in our preliminary studies [14,27]. We also do not expect any study-related adverse events with the pain management surveys. We will monitor adverse events weekly through direct check-in phone calls during the intervention period and monthly during the follow-up period and follow the Good Clinical Practice procedures.

Because there is minimal risk associated with this study, the IRB does not require a Clinical and Translational Science Institute data integrity monitor or data monitoring committee. The principal investigator ([name]) and [name] (study physician) will determine whether an adverse event is expected or unexpected, if it occurs. An adverse event will be considered unexpected if the nature, severity, or frequency of the event is not consistent with the risk information previously described for the study intervention. Aside from the weekly and monthly check-ins, we will ask participants to reach out to the principal investigator or project and data manager, if (severe) adverse events occur in the period between the calls. We will follow all regulations and protocols as outlined by the University of Minnesota’s IRB should this occur.

Our safety monitoring plan includes an independent medical monitor: [name], neurosurgeon at the University of Minnesota, is not associated with this research project and works independently of the principal investigator ([name]). He is not part of the key personnel involved in this grant, nor has he collaborated or copublished with the principal investigator within the past 3 years. He is qualified to review the patient safety data generated by this study because of his unique expertise as a neurosurgeon.

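### The 'good' tier of the safety go/no-go benchmark sets no severity or frequency limit on adverse events from the pain surveys, so the survey arm cannot fail it

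*Protocol article*

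**What the plan says.** Table 2 (Methods, Feasibility Benchmarks) heads its right-hand column "Benchmark (go/no-go criteria"). The 'Program safety' row gives two grades. The upper one is "Excellent safety: no study-related adverse events". The lower one is "good if there are minimal and mild adverse events (eg, muscle soreness) linked to Qigong practice in max 10% of participants", and the sentence then continues "or any adverse events with the pain management surveys", so that the cap and the survey clause read together as "in max 10% of participants, or any adverse events with the pain management surveys".

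Under Ethical Considerations the article states the expectation for the comparator: "We also do not expect any study-related adverse events with the pain management surveys".

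On numbers, the abstract says that "40 adults with SCI-related neuropathic pain (with at least 50% [n=20] having health disparities) will be randomized". Overall Study Design says that "Randomization will be generated by an independent biostatistician", but the article gives no allocation ratio.

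**The concern.** A go/no-go criterion has to be able to return a no-go. The safety row names only 'excellent' and 'good', so its only route to an unfavourable result is an outcome that falls outside 'good'. For Qigong such outcomes exist: events that are more than mild, or events in more than 10% of participants. For the pain surveys none exists, because the clause accepts any adverse events.

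The survey arm's contribution to the safety grade is therefore settled before any data are seen, apart from the choice between 'excellent' and 'good'. The benchmarks are described as set in advance to test the methodology before a larger trial, and the results are to support a grant submission for that trial. A grade that one arm cannot fail tells the reader nothing about that arm.

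A smaller matter in the same cell is that the 10% is a share of 'participants' without saying whether these are the Qigong arm or everyone randomized.

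**Working it through.** **Survey clause.** This part is a matter of reading, not arithmetic.

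| Limb of the 'good' tier | Severity limit | Frequency limit | Result that falls below 'good' |
|---|---|---|---|
| Qigong-linked events | minimal and mild | at most 10% of participants | anything more severe, or more frequent |
| Survey events | none | none ('any') | none |

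To show the range, assume 1:1 allocation, so 20 people in the survey arm. One mild event in 20 grades 'good'. Read literally, 20 of 20 with moderate or severe survey-related events also grades 'good'. The second case is an extreme that shows the clause has no boundary; it is not a forecast.

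The criterion and the stated expectation also fit poorly together. Ethical Considerations expects no study-related survey events, yet the benchmark tolerates an unlimited number.

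**Denominator.** The 10% is a chosen threshold with no calculation behind it, so there is no figure of the plan's to reproduce. Converted to counts:

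- Inputs: 40 randomized (abstract, Methods) and a 10% cap (Table 2). The allocation ratio is not stated; 1:1 is assumed, with 2:1 and 1:2 as the range.
- Qigong arm as denominator at 1:1: 0.10 × 20 = 2 people, and 2/20 = 10% of those exposed.
- All randomized as denominator: 0.10 × 40 = 4 people.
- Those 4 people as a share of the Qigong arm: 4/20 = 20% at 1:1; 4/27 = 14.8% at 2:1 in favour of Qigong; 4/13 = 30.8% at 1:2.

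Effect on the grade at 1:1, from the binomial distribution with n = 20, counting only mild Qigong-linked events:

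| True rate in the Qigong arm | P(at most 2 of 20) | P(at most 4 of 20) |
|---|---|---|
| 10% | 0.68 | 0.96 |
| 20% | 0.21 | 0.63 |

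The two readings would thus give noticeably different grades. Which one is more natural is taken up under the objection.

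**The case against.** **The survey clause is harmless.** The comparator is a two-minute daily questionnaire with no advice component, and the therapy being developed is Qigong, whose limb is bounded on both severity and frequency. This stands as a reason to rate the point modestly. It does not turn 'any' into a criterion.

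**'Minimal and mild' may carry over to the survey events.** The authors may have meant that. The reading is strained, because the qualifiers sit in the Qigong part of the sentence and the survey part opens with its own word, 'any'. Even if severity carried over, no frequency limit would follow.

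**Safety is covered elsewhere.** The same row calls for adverse event assessment and reporting under IRB, GCP and ACTTION guidance, and Ethical Considerations adds an independent medical monitor and prompt forwarding of related events to the IRB and NCCIH. A reader might infer from the benchmark that serious survey events would pass unnoticed, or that the survey arm's grade alone would license the next trial. The article supports neither. What stands is narrower: review and reporting of events do not alter the Table 2 grade.

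**The 10% cap is really 20%.** A reader might infer that the plan doubles its own limit. The documents do not support this. Only people assigned to Qigong can have events linked to Qigong practice, and Table 2 uses the bare word 'participants' for the Qigong arm in its adherence row. Both favour the Qigong-arm denominator. The doubling also needs a 1:1 ratio that the article never gives. What remains is a point of clarity.

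**'Excellent' on zero events is unsafe at this sample size.** A reader might set the exact two-sided 95% upper limit for 0/20, which is 1 − 0.025^(1/20) = 16.8%, against the 10% cap. That comparison fails. 'Excellent' requires no study-related event in either arm, that is 0/40, with an upper limit of 1 − 0.025^(1/40) = 8.8%. In addition, the cap applies to an observed proportion, not to a confidence limit. No criticism of the 'excellent' tier is made here.

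**Conclusion.** The point holds for the survey clause. As written, the 'good' tier places no limit on the severity or number of survey-related adverse events, so the survey arm cannot fall below 'good' on a criterion presented as go/no-go. This rests on the current wording of one table cell and on no numerical assumption; nothing else in the article narrows the clause.

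The denominator is a secondary clarification. Its possible size (4 people instead of 2, or 20% of the Qigong arm instead of 10%) depends on an assumed 1:1 allocation and on the less natural reading of 'participants'; the share runs from about 15% to 31% under 2:1 to 1:2.

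Severity is minor to moderate. A stated decision rule is defective for one arm, but that arm is a low-risk comparator and the handling of individual events does not depend on the grade.

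**What to change.** In the 'Program safety' row, delete the clause that accepts any survey events and state one bounded rule for each arm. The simplest version reuses the row's own limit: 'good' means only minimal or mild study-related adverse events, in at most 10% of the participants allocated to that arm. This also settles the denominator. The survey-arm limit is one the authors have not yet chosen, so they should confirm it, or set another explicit limit on severity and frequency, before final grading.

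The edit is one table cell, with no added burden for participants, but it is not free. The article reports protocol version 2 with no further changes anticipated, and amendments need IRB approval before they are implemented. By September 2025, 36 of the planned 40 had been recruited for aim 2, so a benchmark set in advance would be changed after most participants were enrolled. The change should therefore be dated, given with its reason, and reported as made during the trial. The safety grade could also look slightly less favourable under the bounded rule.
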